#### Physical activity (self-reported) and sitting time

Self-reported activity data will be assessed using a validated and reliable International Physical Activity Questionnaire (IPAQ) short version and work-related IPAQ module from the long version [68, 69].

#### Sleep

Sleep duration and quality will be measured using the valid and reliable Pittsburgh Sleep Quality Index [70]. We will also derive an objective measure of sleep using the GENEActiv activity monitors for study participants who choose to wear them during their sleep [71]. Total sleep time, number of awakenings, sleep onset and offset will be extracted from the device using open source macros [47].

#### Theory-derived psychological constructs

Psychological constructs derived from the motivation and volition theories and habit theory will be assessed using previously-validated and reliable psychometric questionnaires adapted to make reference to physical activity. The measures will include self-report measures of intentions [72], motivation, attitudes [73], outcome expectations [74], perceived behavioural control [73], subjective norms [73], barriers self-efficacy [75], action planning and coping planning [76], self-efficacy, goal facilitation and goal conflict [61]. Habit strength will be measured using the self-report behavioural automaticity index [63, 77]. Individual differences in tendencies to follow routines will be assessed using the personal need for structure scale [78].

#### Depression, anxiety and stress

Validated and reliable Depression, Anxiety and Stress Scale (DASS21) will be used to measure negative affective outcomes [79].

#### Quality of life

Quality of life will be assessed with the widely used, valid and reliable Medical Outcomes Survey - Short Form 12 (MOS-SF12) measure [80].

#### Perceived environmental factors

Participants ratings of the extent to which their home neighbourhood environment is supportive and conducive to physical activity will be assessed with the validated and reliable Physical Activity Neighbourhood Environment Survey (PANES) [81].

#### Internet use and intervention accessibility

Internet use and access will be measured with items developed specifically for this study. Usefulness and satisfaction with the intervention will be measured with the System Usability Scale [82]. Participants’ confidence in their ability to use the internet will be measured with validated and reliable internet self-efficacy scale [83].

### Characteristics of the intervention

Acceptability of the advice provided, intervention delivery and format will be measured with items used in previous studies [66].

### Demographics

Participants will be prompted to self-report a number of key demographic details: age, sex, marital status, ethnicity, education, weight, height, household income, postcode, the number of hours and days worked per week, work level (e.g., clinical nurse manager, registered nurse, patient care assistant), salary brackets associated with each employment level, type of work undertaken (e.g., shift-worker, non-shift worker, mix), and absenteeism in the last 3 months.

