## Abstract

**Background:**

Most people do not engage in sufficient physical activity to confer health benefits and to reduce risk of chronic disease. Healthcare professionals frequently provide guidance on physical activity, but often do not meet guideline levels of physical activity themselves. The main objective of this study is to develop and test the efficacy of a tailored intervention to increase healthcare professionals’ physical activity participation and quality of life, and to reduce work-related stress and absenteeism. This is the first study to compare the additive effects of three forms of a tailored intervention using different techniques from behavioural theory, which differ according to their focus on motivational, self-regulatory and/or habitual processes.

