**Methods/Design:**

Healthcare professionals (*N* = 192) will be recruited from four hospitals in Perth, Western Australia, via email lists, leaflets, and posters to participate in the four group randomised controlled trial. Participants will be randomised to one of four conditions: (1) education only (non-tailored information only), (2) education plus intervention components to enhance motivation, (3) education plus components to enhance motivation and self-regulation, and (4) education plus components to enhance motivation, self-regulation and habit formation. All intervention groups will receive a computer-tailored intervention administered via a web-based platform and will receive supporting text-messages containing tailored information, prompts and feedback relevant to each condition. All outcomes will be assessed at baseline, and at 3-month follow-up. The primary outcome assessed in this study is physical activity measured using activity monitors. Secondary outcomes include: quality of life, stress, anxiety, sleep, and absenteeism. Website engagement, retention, preferences and intervention fidelity will also be evaluated as well as potential mediators and moderators of intervention effect.

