### The present study

There is a need for cost-effective, efficacious behavioural interventions to increase physical activity in healthcare professionals [13]. Research has suggested that theory-based interventions adopting multiple BCTs are effective in increasing physical activity behaviour [31]. Recent research efforts have focused on linking BCTs with underlying theoretical mechanisms of action [44]. However, few studies have systematically examined the efficacy of specific groups of BCTs that are thought to operate through one of the three specified processes (motivational, volitional, and habit-forming) and assessed their independent and additive effects on behaviour change. The purpose of the current study, the Physical Activity Tailored intervention in Hospital Staff (*PATHS*) study, is to evaluate the efficacy of a computer-tailored intervention to increase physical activity and quality of life, and decrease work-related stress and absenteeism, in hospital healthcare workers. The intervention will examine the additive effects of groups of BCTs derived from theories of motivation, volition, and habit on physical activity behavior change. The research is unique as it will provide the first evidence of the efficacy of techniques derived from these three theoretical approaches applied in a workplace context. The study will adopt a randomised controlled design to test and compare the effects of three distinct groups of BCTs derived from theory and focusing different processes of behaviour changes on study outcomes: motivation, self-regulation, and habit formation.

Specifically, the intervention will include motivational techniques to increase motivation and self-efficacy to engage in physical activity, self-regulatory techniques to increase capability and skills to initiate and regulate behaviour change, and habit-based techniques to increase the automatic, non-conscious tendencies to engage in physical activity on presentation of contextual and time-relevant cues. Three intervention conditions are proposed, each defined by the sets of BCTs in an additive design: (1) motivational BCTs; (2) motivational plus self-regulatory BCTs; and (3) motivational plus self-regulatory and habit formation BCTs. The intervention groups will be compared to a control condition that will receive basic non-tailored information about physical activity.

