### Measures

Table 3 describes measures that will be taken during the study, specifying the type of outcome assessed, the measurement tool used, the number of questions included, and the time points when the measures will be administered.

**Table 3 Tab3:** Measures taken at Time 1 and Time 2 and outcomes assessed

Measurement tool	Reference	Number of items		Outcome
		Time 1	Time 2	
		(baseline)	(3 months)	
Survey measures				
Confirmation of eligibility to participate in the study	N/A	8	-	Eligibility
Physical Activity Readiness Questionnaire (PAR-Q)	[45]	8	-	Readiness to undertake PA
Demographics	Commonly used items	14	6	Age, sex, marital status, ethnicity, education, weight, height, house income, postcode
International Physical Activity Questionnaire (short version)	[68, 69]	7	7	Physical Activity
Job-related physical activity	From: International Physical Activity Questionnaire (long version) [68]	8	8	Job-related physical activity
The Pittsburgh Sleep Quality Index (PSQI)	[70]	9	9	Sleep
Theory-relevant determinants of physical activity	Individual items taken from different questionnaires	30	30	Motivation, attitudes towards regular physical activity, outcome expectations, perceived behavioural control, subjective norms, intentions, barriers self-efficacy, action planning and coping planning, self-efficacy, goal facilitation and goal conflict
Self-report behavioural automaticity index	[77]	8	8	Behaviour automaticity
Personal Need for Structure Scale	[78]	12	-	Personal Need for Structure
Physical activity intentions	[72]	3	3	Physical Activity Intentions
Depression Anxiety Stress Scale 21 (DASS 21)	[79]	21	21	Depression, Anxiety, Stress
SF 12	[80]	12	12	Quality of life
Physical Activity Neighbourhood Environment Survey (PANES)	[81]	17	-	Perceptions of the environment in relation to PA
Internet use and access to the intervention	Items developed for this study	-	4	Internet use and access to the intervention
Internet self-efficacy scale	[83]	9	-	Internet self-efficacy
SUS and satisfaction	[82]	-	16	SUS and satisfaction
Physical advice acceptability	[66]	-	15	Physical advice acceptability
Delivery mode usability	[66]	-	5	Delivery mode usability
Usefulness questions	[66]	-	5	Intervention usefulness
Format-related questions	[66]	-	9	Format
Total items		158	158	
Outcome measures and moderators				
Physical activity objectively measured with GENEActiv	[47, 67]	✓	✓	Objectively measured physical activity

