#### Physical activity

The primary outcome will be measured physical activity over a one-week period prior to the intervention (Time 1) and for a further week immediately post-intervention at the three-month follow-up occasion (Time 2) using accelerometers (GENEActiv Ltd.) [47, 67]. Participants will be asked to wear the unit continuously for the seven day period on the non-dominant upper arm to comply with hospital hygiene regulations. The GENEActiv device is water proof and participants will be informed that they are free to choose whether to wear it while swimming, showering, or sleeping. Data will be collected at 60 Hz epoch frequency. Step counts will be derived from the acceleration data using open-source macros and they will be used as proxy for physical activity [47]. Participants will be supplied with a band specifically designed to fasten the monitor to the upper arm.

Secondary outcomes will be assessed at baseline (Time 1) and post-intervention (Time 2), and will include subjective measures of physical activity, sitting time, sleep, depression, anxiety, stress, quality of life, theory-derived correlates of physical activity and self-reported weight. Demographics, perceived neighbourhood environment, personal need for structure, internet self-efficacy, and planning skills/ability will be assessed at baseline (Time 1) only. Secondary outcomes assessed only at the post-intervention stage (Time 2) will include measures of intervention accessibility, usefulness and satisfaction with the intervention, as well as acceptability of the advice provided. Participants’ website usage (e.g., time spent on pages with specific intervention content, number of website visits) will be assessed throughout the study using Google Analytics.

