### Study analysis

The intervention will be evaluated following the recent guidance on process evaluation for complex interventions [86]. Data will be analysed using generalized linear mixed modelling (GLMM) [87] with a 4 (condition: control, motivation, self-regulation, habit) × 2 (time: baseline, 3-month follow-up) mixed-model design, accounting for nesting within hospital. Models will be conducting to compare change between conditions of the primary outcome (physical activity) and secondary outcomes (e.g., theory-derived psychological constructs, DASS21, MOS-SF12, and absenteeism). Mediation analyses will be conducted using path analytic models using Preacher and Hayes’ bootstrapped approach for multiple mediation [88]. Separate path models will be conducted for each condition. Each condition will be represented by a dichotomous dummy-coded variable (0 = did not receive intervention component, 1 = received intervention component). Each condition variable will be set as a predictor of physical activity at follow up with motivation and intention (motivation condition), perceived behavioural control and planning (self-regulation condition), and self-reported habit (habit condition) as multiple mediators in each analysis, respectively. Baseline physical activity will be included as a control variable. Intention-to-treat (baseline carried forward) will be utilised for missing data from drop-out. Other missing data will be imputed using multiple imputation with chained equations [89]. Both intention-to-treat and completers analyses will be reported.

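### The Measures text limits demographics, where absenteeism is collected, to baseline; Table 3, the abstract and the analysis imply a 3-month repeat, and no measurement section schedules one

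*Protocol article*

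**What the plan says.** **Absenteeism as objective and outcome.** The abstract's Background makes it part of the main objective ("to reduce work-related stress and absenteeism"), and The present study repeats the aim ("decrease work-related stress and absenteeism"). The abstract's Methods/Design names absenteeism among the secondary outcomes and says "All outcomes will be assessed at baseline, and at 3-month follow-up". Study analysis fits a 4 (condition) × 2 (time) mixed model to compare change, and includes absenteeism among the "secondary outcomes (e.g., theory-derived psychological constructs, DASS21, MOS-SF12, and absenteeism".

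**Absenteeism as a measurement.** The only description of how it is collected is in Demographics, as a self-reported item: "absenteeism in the last 3 months". The timing paragraph in Measures (under Physical activity) states: "Demographics, perceived neighbourhood environment, personal need for structure, internet self-efficacy, and planning skills/ability will be assessed at baseline (Time 1) only". The same paragraph lists the secondary outcomes taken at both times. Stress, sleep, quality of life and self-reported weight are on that list; absenteeism is not.

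**Table 3.** The demographics row shows 14 items at Time 1 and 6 at Time 2. Its outcome column reads "Age, sex, marital status, ethnicity, education, weight, height, house income, postcode", which names neither absenteeism nor any work-related item.

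**Stress.** The objective, as worded in the abstract, The present study and the Discussion, concerns work-related stress. The only stress instrument is the DASS21, given at both times, which "will be used to measure negative affective outcomes".

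**The concern.** The planned analysis of absenteeism needs a value at both visits. The paragraph that sets measurement timing puts the section holding the absenteeism item at baseline only and does not list absenteeism among the repeated outcomes. Anyone building the Time 2 questionnaire from that paragraph would leave the item out.

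The loss would be complete for this outcome. With one time point there is no condition-by-time contrast to estimate, and a 3-month recall item missed at follow-up is hard to recover later. The primary outcome is not touched.

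The stress issue is separate and smaller. The objective names a construct tied to work, and the instrument measures general negative affect. A DASS21 result can support a statement about stress but not one about stress arising from work.

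**Working it through.** **1. Does Table 3 really repeat demographic items at Time 2?** The inputs are the item counts in Table 3.

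- Time 2, all rows: 6 + 7 + 8 + 9 + 30 + 8 + 3 + 21 + 12 + 4 + 16 + 15 + 5 + 5 + 9 = 158. The stated total is 158, so it is reproduced exactly.
- Time 2 without the demographic items: 158 − 6 = 152, which does not match.

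The 6 is therefore built into the table's total and is unlikely to be a stray entry.

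- Time 1, all rows: 8 + 8 + 14 + 7 + 8 + 9 + 30 + 8 + 12 + 3 + 21 + 12 + 17 + 9 = 166. The stated total is 158. Leaving out one 8-item screening row (eligibility or PAR-Q) gives 166 − 8 = 158. That explanation is an assumption, and nothing here depends on it.

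**2. Is absenteeism among the 14 baseline items?** The Demographics section lists nine personal items (age, sex, marital status, ethnicity, education, weight, height, income, postcode). It then lists hours and days worked, work level, salary bracket, type of work, and absenteeism.

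- Counting hours and days as one item: 9 + 5 = 14, which matches Table 3.
- Counting them as two: 15, which does not.

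On the first count, absenteeism is already inside the Table 3 row and the outcome column is abbreviated (9 of 14 named).

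**3. Is it among the 6 repeated items?** Table 3 does not identify the six. Weight plus the five work-related items (hours and days, work level, salary bracket, type of work, absenteeism) would make 1 + 5 = 6. That fits, but it is inference.

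**4. Places that bear on Time 2 absenteeism, side by side.**

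| Place | What it implies for Time 2 |
|---|---|
| Abstract, Methods/Design | Yes: all outcomes at both times, absenteeism named |
| Study analysis | Required: change is modelled |
| Table 3 | Possible: 6 demographic items, not identified |
| Demographics section | Silent on timing |
| Measures, timing paragraph | No, read literally: demographics at baseline only, absenteeism not on the repeated list |

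The timing paragraph also conflicts with itself on weight. Weight is a demographic item in both the Demographics section and Table 3, yet the paragraph lists self-reported weight as taken at both times. So the baseline-only sentence does not hold for every item in the section. The exception is written out for weight and not for absenteeism.

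**5. What the literal reading would cost.** Follow-up absenteeism would be missing for everyone. With 192 recruited and 30% drop-out, that includes 192 × 0.70 ≈ 134 people expected to attend. This figure applies only if the baseline-only sentence is followed.

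**6. Stress.** No arithmetic applies. Table 3 and the Measures text contain no work-specific stress scale or item; the DASS21 stands alone. The abstract's list of secondary outcomes and the timing paragraph call the outcome simply stress, so only the objective carries the work-related qualifier.

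**The case against.** The strongest reply is that absenteeism is a named outcome with a stated schedule. The abstract places every outcome at baseline and 3 months, the analysis models its change, and Table 3 repeats six demographic items. The weight example shows that being listed under demographics does not make an item baseline-only. A 3-month recall suits a 3-month visit. A journal article may also leave the identity of the six repeated items to the full protocol or the questionnaires.

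Most of this stands. It makes a Time 2 measurement the likelier intention, and item-level detail alone would not be a finding. It does not remove the contradiction, because the article states a timing rule for demographics that its own table and analysis do not follow.

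A reader might go further and infer that absenteeism is measured only at baseline, or that two stated objectives have no matching outcome. The documents do not support either. Absenteeism is a named outcome whose follow-up collection is contradicted and unconfirmed, which is different from absent. Stress is measured at both times, so that issue is one of construct labelling. A reader might also infer that a DASS21 result will be reported as an effect on work-related stress. Nothing in the article says how the result will be reported, and Implications speaks only of stress reduction in hospital workers.

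**Conclusion.** The inconsistency is real and should be corrected. The baseline-only sentence for demographics conflicts with Table 3 (158 items with the six, 152 without), with the abstract's timing statement and with the planned analysis of change. No measurement section explicitly schedules absenteeism at Time 2, although Table 3 and the abstract suggest that this was meant.

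The consequence is conditional. If the sentence is followed, the absenteeism analysis cannot be run for any participant; if Table 3 and the abstract are followed, and absenteeism is one of the six items, nothing is lost. Matching the 14 items to the Demographics list assumes that hours and days worked form one item, and which six are repeated is unknown from this document.

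The stress mismatch is a lesser point. It limits what may be concluded and leaves the measurement itself intact. Neither issue affects the primary outcome.

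**What to change.** - In the timing paragraph of Measures, add absenteeism (3-month recall) to the secondary outcomes assessed at Time 1 and Time 2.
- In the same paragraph, replace the blanket baseline-only statement for demographics with one that agrees with Table 3, stating which six items are repeated.
- In Table 3, name absenteeism in the existing demographics row. A new row could count the item twice, since it may already be among the 14.
- In the abstract, The present study and the Discussion, word the objective as stress measured by the DASS21, and draw no conclusion specific to work.

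The cost is protocol wording and, if absenteeism turns out not to be among the six, one more questionnaire item at Time 2 with the table total adjusted. The downside is a narrower claim about stress.

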### Adverse effects

Participants will be encouraged to report any adverse effects they may experience during their participation in the intervention over the email or phone call.

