Healthcare professionals often exhibit unhealthy lifestyle behaviours with work-related stress identified as the most frequently-cited reason [11]. Professionals report that hospitals are a highly stressful work environment, and irregular shift work often places an additional strain on the hospital employees [12]. Sleep patterns and sleep quality among healthcare professionals were insufficient for good health [13] and physical activity is a recognised means to improve sleep quality [14]. In addition, nurses are prone to suffer lower back pain [15] and physical activity is recommended to this occupational group for managing back pain. As such, there is strong rationale for promoting physical activity among healthcare professionals.

The workplace is reported as a suitable environment for making changes in the physical activity and improving health of employees [16]. Increased participation in physical activity in healthcare professionals can be promoted using behavioural interventions which utilise persuasive strategies and techniques to encourage individuals to change their behaviour (e.g., goal setting, planning, providing social support) [17, 18]. Such interventions have been shown to be effective in promoting increased uptake and maintenance of physical activity, including in the workplace [19–21], hence they may be suitable for promoting physical activity to healthcare professionals.

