### Study design

The *PATHS* study is a pragmatic four-group intervention trial adopting a randomised control design with assessments of primary and secondary outcomes at baseline and 3-month follow-up time points (see Fig. 1). We chose randomisation of individuals within hospitals (rather than randomisation of hospitals or wards) because individual randomisation was more efficient and more feasible with continuous recruitment of the participants; program was delivered to individuals rather than groups so contamination across intervention groups was not considered a major risk [46]. The project comprises three intervention conditions and a no intervention condition, in which participants receive information about the study only. This will serve as a control condition. Each condition includes a group of theory-based BCTs designed to test the additive effects of the specific BCT groups on study outcomes:
**Control condition** – provision of information about physical activity only
**Motivation condition** – provision of information + motivational BCTs
**Self-regulation condition** – provision of information + motivational BCTs + self-regulatory BCTs
**Habit condition** – provision of information + motivational BCTs + self-regulatory BCTs + habit formation BCTs

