After the second meeting, participants will be emailed a personalised login/password, and link to the website so they are able to login to the web-based *PATHS* study platform used to deliver the tailored intervention messages. Participants will be automatically randomly allocated online in an equal ratio to one of the four possible study conditions; a block randomisation will be used with block size of 16. If allocated to one of the three intervention conditions, they will be able to complete the first intervention session on the website immediately after completing the baseline assessments. If allocated to the control condition, they will receive an email directing them to the *Library* site for physical activity relevant information. The *Library* is a sub-section of the website with non-tailored evidence-based information about physical activity,

Across all conditions, participants will be encouraged to use and interact with the web-based *PATHS* platform for three consecutive months, completing sessions every fortnight. At the end of month three, participants will meet with the researcher and will be provided with a GENEActiv activity monitor to be worn for one week immediately post-intervention to assess physical activity. Participants will meet with the researcher again one week after they received the activity monitor to complete the post-intervention questionnaires and return the activity monitor (Time 2). All researchers collecting the data will be blinded to the allocation of participants’ study condition.

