The platform uses if-then algorithms to provide tailored feedback based on the participant’s responses. The feedback will be drawn from a database of messages incorporating feedback combinations tailored to the participant’s condition and responses to prompts for information on the website. The platform will store participants’ responses for each session, permitting tailoring of the intervention to the responses from the current session, as well as to responses from previously completed surveys. For instance, graphs displayed to the participants will include changes in physical activity throughout the intervention.

In addition, all groups, with the exception of the control group, will receive weekly text messages sent at the same time each week to provide further condition- and session-relevant feedback based on their most recently completed session and including a short summary of key points. There will be three introduction messages and each session has two session specific text messages, followed by a final concluding message. Participants will also receive regular fortnightly reminders to login to the intervention website when a new session is available sent via email. Up to three reminders will be sent per session (one every four days).

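### The only adverse-effect route described is a report the participant starts, over a window that is unclear for controls, so counts by arm would be a weak basis for a safety statement

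*Protocol article*

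**What the plan says.** The Adverse effects section is one sentence: "Participants will be encouraged to report any adverse effects they may experience during their participation in the intervention over the email or phone call". It sets the route (email or telephone, started by the participant) and the window (participation in the intervention).

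Study design describes the arms thus: "The project comprises three intervention conditions and a no intervention condition, in which participants receive information about the study only". The list that follows in the same section gives controls information about physical activity.

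Intervention delivery states that "all groups, with the exception of the control group, will receive weekly text messages sent at the same time each week", and then gives the number: "There will be three introduction messages and each session has two session specific text messages, followed by a final concluding message". The fortnightly surveys with tailored feedback are described for the three intervention groups.

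The follow-up visit is described without distinction by arm: "Participants will meet with the researcher again one week after they received the activity monitor to complete the post-intervention questionnaires". Table 3, introduced as the description of the measures to be taken, totals 158 items at Time 2. None of its rows is labelled as a measure of adverse effects or injury.

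**The concern.** The trial asks insufficiently active hospital staff to become more active, so injury and musculoskeletal complaints are foreseeable. A route that depends on participants getting in touch tends to miss events. It is also sensitive to how often each arm hears from the study, and here that differs by design.

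Two things are at stake. A low count could reflect few events or little reporting. A difference between arms could reflect a difference in harm or in reporting. Any sentence on safety placed beside the efficacy result would carry both uncertainties, and the data could not separate them. The missing information is hard to recover once follow-up has ended.

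**Working it through.** The document gives no harm rate and no reporting probability, so there is no figure of its own to reproduce. The check has four steps.

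**1. Window.** Study design calls control a no-intervention condition, which would leave it outside a window defined by participation in the intervention. Against this, Intervention delivery has participants in every condition logging in to the web-based intervention, and Procedure encourages use of the platform for three months in every condition. The Adverse effects sentence itself speaks of participants without limiting them by arm. On balance controls appear to be included, but the wording leaves it to the reader.

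**2. Scheduled remote contact** (from Intervention delivery).
- Texts per intervention participant: 3 introductory + 6 sessions × 2 + 1 closing = 16. Texts per control participant: 0.
- Tailored fortnightly sessions: 6 in each intervention arm, none in control.
- Session reminder emails: at most 3 × 6 = 18. Whether controls receive any is unclear, so they are not counted in the contrast.

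**3. Effect of unequal reporting.** Let p be the true risk, equal in all arms, and r_int and r_ctl the probabilities that an event is reported. With 3 × 48 = 144 intervention and 48 control participants (Sample size), expected reports are 144·p·r_int and 48·p·r_ctl, and the apparent risk ratio is r_int / r_ctl. The values p = 10% and all reporting probabilities below are assumptions for illustration.

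| r_int | r_ctl | Expected reports (intervention v control) | Apparent risk ratio |
|---|---|---|---|
| 50% | 50% | 7.2 v 2.4 | 1.0 |
| 70% | 50% | 10.1 v 2.4 | 1.4 |
| 60% | 30% | 8.6 v 1.4 | 2.0 |
| 30% | 60% | 4.3 v 2.9 | 0.5 |

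True events in every row are 14.4 v 4.8. The ratio does not depend on p. Reporting can also hide a real difference: true risks of 20% v 10% with reporting of 30% v 60% give 0.20 × 0.30 = 6% v 0.10 × 0.60 = 6%.

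**4. What a low count can exclude.** With zero reports among 144, the one-sided 95% upper bound on the reported rate is 1 − 0.05^(1/144) = 2.06%. If all events are reported, that also bounds the true rate. If only 30% are reported (assumption), the bound is 2.06 / 0.30 = 6.9%.

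For the remedy, the article's 30% dropout, assumed equal across arms, means that about 0.30 × 144 = 43 intervention and 0.30 × 48 = 14 control participants would not be reached by a question asked at Time 2 alone.

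**The case against.** The strongest reply is that this is a low-risk, PAR-Q-screened, web-delivered programme described in a condensed article, and that no harm endpoint, hypothesis or between-arm test appears under Study hypotheses or Study analysis. Nothing planned is invalidated. Participants are encouraged to report, so the route is not wholly unprompted. In-person visits are the same in every arm, a facilitator is open to all, and nothing says that the texts invite adverse-effect reports. DASS-21, SF-12, sleep and absenteeism are collected systematically. All of this stands, and it limits the point to the quality of the reported counts. It does not remove the point: the article states a method, and the systematic measures named are not presented as a record of injuries.

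Three stronger readings are tempting and are not supported:
- **That controls have no reporting window.** A reader might infer this from "The project comprises three intervention conditions and a no intervention condition", but Procedure and Intervention delivery treat controls as users of the platform.
- **That no questionnaire item asks about pain.** Table 3 lists instruments and item counts, not item wording. It supports only the statement that no listed measure is for adverse effects or injury.
- **That no valid safety statement is possible.** With equal reporting the ratio is undistorted, as the first row of the table shows. The documents do not establish that reporting would be unequal.

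Nor should the remark that "nurses are prone to suffer lower back pain" be read as an expected harm of the programme. The Background goes on to say that activity is recommended for managing back pain.

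**Conclusion.** The point holds as a weakness in harm ascertainment with a cheap remedy. The described route is participant-initiated, its window is worded ambiguously for controls, and scheduled remote contact is unequal (16 texts v 0). Reported counts are likely to be incomplete, by an amount the document cannot fix, and are a weak basis for any statement by arm.

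The apparent risk ratios of 0.5 to 2.0 and the 6.9% bound rest entirely on assumed reporting probabilities, with an assumed 10% risk behind the event counts. They show what could happen and estimate neither the size nor the direction of bias. The primary efficacy analysis is unaffected.

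**What to change.** 1. Keep the email and telephone route, and reword its window to run from allocation to Time 2 in all four conditions.
2. Add one or two self-completed items to the existing Time 2 questionnaire, identically worded in every arm, on any new injury, pain or illness since baseline and whether it limited activity or led to care.
3. Send the same item once, by email or text, to anyone who withdraws or misses Time 2.
4. Report solicited events by arm with the number who answered as denominator, and list spontaneous reports separately by arm.

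The cost is a slightly longer questionnaire, one automated message to non-attenders and a minor amendment. The event count will probably be higher than under spontaneous reporting alone, and the report should say why. Self-completion on the tablet helps to keep the data collectors blinded.
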